## Abstract

**Background:**

Cancer-related fatigue (CRF) is a common and distressing symptom of cancer and/or cancer treatment that persists for years after treatment completion in approximately one third of cancer survivors. Exercise is beneficial for the management of CRF, and general exercise guidelines for cancer survivors are available. There are multiple potential pathways by which exercise improves CRF, and cancer survivors with CRF are diverse with respect to cancer type, treatments and experienced side effects. While the general exercise guidelines are likely sufficient for most cancer survivors, tailoring of exercise interventions may be more effective in those with persistent fatigue. The primary aim of this research is to investigate the effect of a traditional vs. tailored exercise intervention on CRF severity in cancer survivors with persistent CRF.

**Methods/design:**

Cancer survivors (≥ 3 months and ≤ 5 years since primary treatment) who score ≤ 34 on the Functional Assessment of Chronic Illness Therapy Fatigue Scale (FACIT-F) will be randomly allocated to one of two parallel treatment arms: traditional (active control) and tailored exercise. Participants in the traditional exercise group will engage in aerobic and resistance exercise that is consistent with exercise guidelines for cancer survivors. The tailored exercise group will be prescribed an intervention designed to address individual deficits identified at baseline, such as loss of muscular strength, cardiorespiratory deconditioning or sleep disturbance. Participants will be assessed before and after the intervention for CRF severity and other patient-reported outcomes, neuromuscular function and fatigue in response to whole-body exercise, sleep quantity and quality, physical activity levels, cardiorespiratory fitness and blood biomarkers.

**Discussion:**

To our knowledge, this will be the first study to compare the effects of a traditional vs. tailored exercise intervention on CRF severity in cancer survivors with persistent CRF. Using physiological, behavioural and patient-reported outcomes, this study will add to the current knowledge about both the factors contributing to CRF, and the potential reduction in CRF severity with an exercise intervention.

**Trial registration:**

The study is registered at ClinicalTrials.gov (NCT03049384), February, 2017.

**Electronic supplementary material:**

The online version of this article (10.1186/s12885-018-4668-z) contains supplementary material, which is available to authorized users.

## Background

Fatigue, characterised by a subjective sense of tiredness, is a common and distressing symptom associated with cancer or cancer treatment [1]. Cancer-related fatigue (CRF) differs from fatigue experienced by healthy individuals (e.g. following intense or prolonged exercise, or sleep deprivation), in that it is non-transient and less likely to be relieved by rest. With chronic fatigue, which is a hallmark of multiple pathologies, daily activities can be limited or associated with undue effort [2]. This is the case for CRF, which has been defined from an experiential perspective as a distressing, persistent sense of physical, emotional, and/or cognitive tiredness or exhaustion that is not proportional to recent activity and interferes with usual functioning [3]. Because there is no objective surrogate measure of CRF in humans, its severity is assessed as a patient-reported outcome. A number of CRF scales have been used for this purpose, and the Functional Assessment of Chronic Illness Therapy Fatigue Scale (FACIT-F) [4], a 13-item self-report questionnaire which delineates the physical and functional consequences of CRF, is widely recommended [5]. Alongside self-report, measures of physiological, behavioural and/or psychosocial ‘performance’ can supplement our understanding of fatigue as a symptom [6].

The majority of cancer patients will experience CRF during primary treatment, and this often improves or returns to baseline levels after treatment completion. However, one-third of cancer survivors are estimated to have clinically significant CRF which persists for months and years after cancer treatment [7]. This estimate of CRF is predominantly from breast cancer survivors [8], and it may be higher in other tumor groups (e.g. [9]). Considering the incidence of cancer (for example, 206,200 new cases were estimated for 2017 in Canada) and 60% five-year survival estimates (from people diagnosed between 2006 and 2008) [10], the prevalence of cancer survivors with CRF is likely to increase. CRF results in increased utilization of health care resources [11], impacts return to work, and reduces the capability to work [12]. Furthermore, CRF leads to a reduction in the health-related quality of life (HRQL) of cancer survivors [13]. Accordingly, refining or developing evidence-based interventions to alleviate CRF and its impact on functioning and HRQL is a priority for future research [14, 15].

Although the etiology of CRF is under investigation, recent evidence indicates a number of possible mechanisms. In the past decade, the pathogenic processes associated with CRF during or after treatment have been investigated using blood biomarkers and genomic variates [16, 17]. This research has led to the hypothesis that CRF involves multiple (and interacting) biological processes that result from cancer and/or cancer treatment [16]. These include alterations in the cellular immune response, hypothalamic–pituitary–adrenal axis dysfunction and inflammation [18, 19]. A number of physiological alterations and a resultant decline in physical function may be related to CRF, where cancer cachexia [20], other neuromuscular complications [21] and cardiorespiratory deconditioning [22] may contribute. These may be induced by cancer and/or cancer treatment and compounded by physical inactivity during/after treatment (where physical inactivity may also be a behavioural mediator of other alterations such as weight gain). CRF is also influenced by psychosocial factors, such as self-efficacy [23]. Furthermore, cancer survivors with CRF may also be experiencing chronic sleep disturbance as part of a multi-symptom cluster [24]. Given this range of potential contributing factors, investigating, and indeed treating the cause of CRF is challenging. There is minimal evidence of efficacy for any pharmacological treatment for CRF after cancer treatment [25]. Clinicians are guided to screen for a primary cause in the event that CRF is secondary to, for example, anemia, mood disorders or pain [26, 27]. However, where CRF is not resolved in this way (i.e. with treatment of a co-morbidity) and does not recover in the first few months after treatment, it may persist as a primary symptom indefinitely.

A number of behavioural interventions have been investigated for the improvement of CRF in adults (e.g. [28]), but there is widespread agreement the most beneficial intervention is exercise ([29–31]). However, a systematic review of several meta-analyses recently highlighted that although effects are in the direction of benefit, the magnitude of the effect of exercise on CRF varies substantially, such that caution is warranted when drawing definitive conclusions about exercise and CRF [32]. CRF is often a secondary rather than primary outcome of randomized controlled trials, and participant level of CRF at baseline is not necessarily clinically relevant, meaning that the effect of exercise on CRF may actually be diluted [32]. In addition, exercise interventions may not be optimally designed with an improvement in CRF as the target. Nevertheless, due to numerous health benefits, exercise should be part of standard care for cancer survivors, and the American College of Sports Medicine (ACSM) has published specific recommendations for exercise and CRF [33]. In accordance with other published guidelines [34–37], a combination of aerobic and resistance training is recommended, and the health-related physical activity guidelines for the general population are considered appropriate for most cancer survivors (with modifications as necessary for cancer-related side effects). However, it has also been suggested that this ‘one size fits all’ approach may be too generic, particularly in regards to the treatment of persisting side effects such as CRF [38].

Given the lack of pharmacological targets for CRF, and the wider evidence base for exercise as medicine in chronic diseases [39], the potential for improvement in CRF with exercise warrants further evaluation. CRF has been reported in many tumour groups, following a range of (often multi-modal) cancer treatments, meaning that it is likely that cancer survivors present with diverse physiological profiles (and/or deficits) prior to beginning an exercise intervention. Therefore, improvement in specific physiological parameters on an individual basis (such as cardiorespiratory fitness [40]) is a potential target for optimizing the improvement in CRF with exercise. By prescribing an intervention that is tailored to the individual and based on a range of pre-intervention data, the effectiveness of the intervention for the improvement in CRF may be enhanced. The initial data could also include an assessment of baseline sleep quality and quantity, where the potential reciprocal relationship between CRF and sleep disturbance deserves attention because an improvement in CRF with exercise may be related to improvements in sleep [23]. To date, the effect of exercise on sleep in cancer survivors has primarily been assessed using self-report questionnaires, despite differences when compared to objective measures such as actigraphy [41]. Few studies have identified cancer survivors with both CRF and sleep disturbance at baseline prior to an exercise intervention [42]. As such, the relationship between sleep disturbance, CRF and exercise is yet to be fully elucidated [43].

Although some physiological parameters have been associated with CRF, the neuromuscular correlates of CRF have received less attention. Fatigue has been considered under two distinct domains: the perceptions of fatigue (subjective sensations as in CRF) and performance fatigability (objective changes in task performance) [44, 45]. These domains are not mutually exclusive, and investigating performance fatigability may inform the discussion about the improvement of CRF with exercise [46]. One method used to investigate performance fatigability involves firstly measuring the force-generating capacity of a muscle or muscle group, as part of an assessment of neuromuscular function. Next, the participant performs a motor task that results in a reduction in force-generating capacity, i.e. neuromuscular fatigue. In combination with electrical and magnetic stimulation techniques, the central and peripheral contributions to neuromuscular fatigue can be appraised [47]. One such technique is transcranial magnetic stimulation (TMS), a non-invasive and safe method of brain stimulation that is widely used to stimulate the motor cortex in clinical settings [48]. TMS has been used to assess central alterations and fatigue in other chronic conditions [49–51], but to our knowledge, has not yet been used as an investigative tool in cancer survivors.

The measurement of neuromuscular function or fatigue in cancer survivors is relatively rare, with < 10 studies published on the topic [52–59]. The majority of these investigated participants with advanced cancer, who were on [56–58] or off [52–54] active treatment. To summarise the findings, these studies provide evidence that (i) cancer survivors with CRF are unable to sustain submaximal sustained [52–54] or intermittent [55, 56] isometric contractions for as long as matched controls; (ii) early task disengagement occurs with less evidence of peripheral fatigue (i.e. less disturbance to muscle contractile properties) [52, 54, 55] and (iii) central mechanisms may contribute more to the decision to terminate exercise in cancer survivors with CRF compared to matched controls [52, 53]. The evidence for the greater contribution of central mechanisms in these studies is mostly indirectly inferred [e.g. from electromyography or finding (ii)], and only one study [59] used the interpolated twitch technique to measure a reduction in voluntary activation [60] that is the current standard for the measurement of central fatigue. The majority of these studies used measurements in the upper limb [52–55, 58] and/or sustained isometric contractions as the motor task [52–54, 57, 59]. This is of limited functional relevance in regards to daily activities, particularly locomotion. In order to investigate dynamic exercise involving large muscle groups, our lab has developed an ergometer that allows a comprehensive measurement of neuromuscular fatigue before, during and immediately after (cycling) [61], which could be used to inform current understanding of the link between the neuromuscular system and CRF.

In summary, while generic exercise recommendations are likely sufficient for the majority of cancer survivors after treatment, tailoring of interventions may be warranted in cancer survivors with persistent CRF. Indeed, it has previously been suggested that interventions should be tailored according to the specific health outcome [62]. Here, we propose a comprehensive pre-intervention assessment including a number of pathways by which exercise may alleviate CRF, via improvements in physiological parameters or sleep. Based on objective assessments including cardiorespiratory fitness, neuromuscular function and sleep (actigraphy), a tailored exercise intervention will be designed based on individual deficits or areas for improvement. The primary aim of this research is to investigate the effect of a traditional vs. tailored 12-week exercise intervention on self-reported CRF severity (FACIT-F score) in cancer survivors with persistent CRF. We hypothesize that there will be an improvement in CRF after the exercise intervention in both groups, and that the improvement will be greater in the tailored vs. traditional exercise intervention.

## Methods/design

This study is a prospective randomized controlled trial with a two-armed parallel design and 1:1 allocation ratio. Flow through the study is presented in Fig. 1. This study has been approved by the Health Research Ethics Board of Alberta Cancer Committee (HREBA.CC-16-10-10). The approved study will be reviewed annually by the HREBA.CC until completion. Any amendment to the protocol which may impact on the conduct of the study will require formal modification and approval by the HREBA.CC prior to implementation, and will be described transparently in subsequent reports. The study will be performed according to the Declaration of Helsinki. The study was registered at ClinicalTrials.gov before recruitment of the first participant (NCT03049384, first posted in February, 2017). The research will be conducted at a single site (Faculty of Kinesiology, University of Calgary, Alberta, Canada). This study protocol is written in accordance with the SPIRIT guidelines [63] (SPIRIT Checklist provided in Additional file 1).

**Fig. 1 Fig1:**
[figure not shown]
Flowchart of the study design

### Study population

The majority of research in exercise and cancer has been conducted in female breast cancer survivors due to high prevalence and survival estimates [10]. However, CRF is not unique to a specific tumour group or cancer-treatment type. Furthermore, demographic and clinical characteristics do not moderate exercise-induced improvements in other patient-reported outcomes such as physical function and HRQL [64]. Our intention is to offer this program as widely as possible to a heterogeneous group of cancer survivors who are experiencing CRF after treatment. Therefore, male and female cancer survivors aged 18–75, following any cancer diagnosis and cancer-treatment type, will be recruited for the study. Potential participants will be screened for study inclusion using a score of CRF severity using the FACIT-F questionnaire [4] (where a score of ≤34 is the recommended cut-off point for the diagnosis of CRF [65]). Additional inclusion and exclusion criteria are presented in Table 1.

**Table 1 Tab1:** Inclusion and Exclusion Criteria

Inclusion Criteria	Aged ≥ 18 and ≤ 75 years
	FACIT-F score ≤ 34
	Completion of primary treatment in ≥ 3 months and ≤ 5 years from enrolment
	Approval received from CSEP-CEP and/or physician
	Command of the English language and ability to understand instructions related to the study procedures
Exclusion Criteria	Contraindication to experimental procedures and/or exercise
	Previously diagnosed as having sleep apnea or anemia
	Currently participating in a structured exercise program or another clinical trial
	Participant is pregnant

*CSEP-CEP* Canadian Society for Exercise Physiology Certified Exercise Physiologist, *FACIT-F* Functional Assessment of Chronic Illness Therapy-Fatigue, *TMS* transcranial magnetic stimulation

### Sample size

An a priori sample size estimation was performed using G*Power 3 (v3.1.2–3.1.9 [66]). The hypothesis was treated as a time × treatment (within-between) interaction for the primary outcome measure of score on the FACIT-F. A standardized mean difference of 0.44 was used, as reported in a 2012 Cochrane review for comparisons of CRF following an exercise intervention or control, from a total of 539 cancer survivors after anti-cancer therapy [29]. Using an α level of 0.05, a 1 - β of 0.8, the total sample size was calculated as 44. Potential loss to attrition was estimated as 15%, based on previous reports from supervised exercise interventions in cancer survivors post-treatment (e.g. [67]), and thus the total sample size was calculated as 52.

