### Intended statistical analysis

Data will be analysed after data collection is complete, and no interim statistical analysis will be performed. Descriptive statistics will be used for demographic and clinical variables measured at baseline for each group. Frequencies and percentages will be used for categorical variables and the mean ± standard deviation (or median and range) will be used for continuous variables. To account for any differences in loss to follow up between groups, the primary analysis will be conducted on an intention-to-treat basis. For the primary outcome of FACIT-F score between treatment arms over time, data will be analysed with linear mixed models using R [123] and lme4 [124]. “Treatment arm” will be included as a fixed effect and “participant” as a random effect. Parameters will be estimated using restricted maximal likelihood. The Kenward-Roger approximation for degrees of freedom will be used when evaluating the significance of effects. This produces optimal type I error rates (neither anti-conservative nor overly sensitive to sample size) [125]. Secondary analyses will be performed to assess adjustments for protocol deviations (per protocol analysis). Statistical code will be made openly available upon publication of the results. A minimum of a 3-point difference in FACIT-F score will be considered clinically relevant [126]. For secondary outcomes that are assessed pre- and post-intervention only (e.g. neuromuscular measures, sleep parameters, blood biomarkers), two-way mixed design ANOVA will be used (group [tailored vs. traditional] × time [pre- vs. post-intervention]). In this case, missing data will be dealt with using list-wise deletion. Following a significant interaction, pairwise comparisons will be conducted with a Bonferroni adjustment. The threshold for rejecting the null hypothesis will be *p* < 0.05. For main and interaction effects, partial eta squared will be computed as an effect size estimate. Effect sizes for pairwise comparisons will be reported as Cohen’s *d* [127, 128]. This will be supplemented with 95% confidence intervals for mean differences. Further exploratory analysis will be labelled as such in later reporting.

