As this is a single-site study, participants must be able to regularly travel to the University of Calgary, such that it is only feasible for cancer survivors who live locally to participate. We recognise that this is a limitation of the study. In terms of reducing barriers to recruitment for people who live locally, parking costs at the site will be reimbursed. However, participants must also have the time available to participate in an exercise intervention. As the time post-treatment is up to five years, it is anticipated that a number of potential participants will be struggling with CRF after having returned to work and/or while also caring for dependents. To help with overcoming this barrier, exercise sessions will be offered with a large degree of flexibility in regards to the day of the week and the exercise time, which will also be an important factor in regards to participant retention.

In this study, the traditional exercise group was designed as an active control, and considered to be an appropriate comparator to the (experimental) tailored exercise group. A ‘no exercise’ wait-list control was not included in the study design due to the established benefit of exercise on CRF [29–31]. We did not consider it necessary to confirm that an improvement in CRF with exercise was superior to an improvement due to, for example, an additional 3–4 months in the passage of time since cancer treatment. Due to the difficulties in blinding, the active control has been designed to not only be broadly consistent with published guidelines, but to be equivalent to the experimental group on non-specific conditions (that may influence the primary outcome, which is a perceptual construct) such as expectancy, social support during exercise or attention from the exercise specialist [129]. The continuous enrolment strategy is due to the anticipated difficulty in recruiting a single large cohort of eligible and interested cancer survivors who meet the CRF-severity criteria and are able to commit to the intervention. However, parallel groups will also control for potentially confounding variables such as seasonal variations in Calgary, Alberta.

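### The sample size rests on an exercise-versus-control effect of 0.44, which the protocol does not justify as the difference between tailored and traditional exercise

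*Protocol article*

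**What the plan says.** The Sample size section of the protocol article takes its planning effect, 0.44, from a published review. The contrast behind that figure is described there as "for comparisons of CRF following an exercise intervention or control, from a total of 539 cancer survivors after anti-cancer therapy". The section then enters this effect for the trial's own hypothesis: "The hypothesis was treated as a time × treatment (within-between) interaction for the primary outcome measure of score on the FACIT-F". The result is "Using an α level of 0.05, a 1 - β of 0.8, the total sample size was calculated as 44", raised to 52 for 15% attrition.

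The contrast under test is described elsewhere. The last paragraph of the Background sets traditional against tailored exercise, expects fatigue to improve in both groups, and expects the improvement to be larger with tailoring. The Discussion states that "the traditional exercise group was designed as an active control, and considered to be an appropriate comparator". It adds that a no-exercise wait-list arm was left out because the benefit of exercise is already established. The Tailored exercise group section keeps session frequency and total duration the same in both arms.

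The Intended statistical analysis section gives one threshold in scale units: "A minimum of a 3-point difference in FACIT-F score will be considered clinically relevant". It does not say whether this is a difference between arms or a change within a person, and the Sample size section does not use it.

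**The concern.** An effect of 0.44 for exercise against control describes what exercise does. The trial asks what tailoring adds when the comparison group also exercises on a guideline programme. These are different quantities, and the protocol offers no argument that the second is as large as the first.

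At stake is how the 80% power is read. A reader will take it to apply to tailored against traditional exercise. If the true increment is smaller, a non-significant result is likely even when tailoring helps, and it could be misread as evidence that tailoring adds nothing. The closing summary of the Discussion links this comparison to referral to a clinical exercise physiologist, so the reading has consequences.

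**Working it through.** **1. Reproducing the protocol's figure.** From the Sample size section: effect 0.44, α 0.05, power 0.80, within-between interaction, G*Power 3. From the Methods/design opening: two arms, 1:1. Not stated, and assumed here: f = d/2 = 0.22, m = 2 measurements, correlation ρ = 0.5.

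Noncentrality λ = f² × N × m / (1 − ρ), with 1 and N − 2 degrees of freedom.

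- N = 44: λ = 0.22² × 44 × 2 / 0.5 = 8.52; critical F(1, 42) = 4.07; power 0.814.
- N = 42: power 0.795, which is below target. So N = 44 is reproduced.
- Attrition: 44 / 0.85 = 51.8, rounded up to 52, as stated.

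The arithmetic follows from these inputs. The point here is the effect that was entered.

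**2. Changing only the effect.** The documents give no effect for tailored against traditional exercise, so the increment is taken as an assumed fraction of 0.44. Everything else stays as in step 1, with N = 44.

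| Increment | d | f = d/2 | λ | Power |
|---|---|---|---|---|
| all of 0.44 | 0.44 | 0.22 | 8.52 | 0.81 |
| three-quarters | 0.33 | 0.165 | 4.79 | 0.57 |
| half | 0.22 | 0.11 | 2.13 | 0.30 |
| a quarter | 0.11 | 0.055 | 0.53 | 0.11 |

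This table isolates the present point.

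**3. What 44 completers offer against 3 points.** Here the 3-point threshold is applied between arms, with 22 per arm and a baseline-adjusted comparison. The SD (7 to 10) and the pre-post correlation r (0.5 to 0.8) are assumptions; the protocol gives neither.

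Residual SD = SD × √(1 − r²). Standard error = residual SD × √(2/22). 95% half-width = 2.02 × standard error (t on 41 degrees of freedom). Power is from the noncentral t with noncentrality 3 / standard error.

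Example, SD 7 and r = 0.5: residual SD 7 × √0.75 = 6.06; standard error 6.06 × 0.3015 = 1.83; half-width 3.7; noncentrality 3 / 1.83 = 1.64; power 0.36.

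| r | Power, SD 7 to SD 10 | 95% half-width in points, SD 7 to SD 10 |
|---|---|---|
| 0.5 | 0.36 to 0.20 | 3.7 to 5.3 |
| 0.7 | 0.49 to 0.28 | 3.0 to 4.3 |
| 0.8 | 0.64 to 0.37 | 2.6 to 3.7 |

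Step 3 works directly on the score difference and does not use f = d/2. Its powers are therefore not comparable with the 0.81 of step 1, and the gap must not be credited to the choice of contrast. By direct calculation with 22 per arm and r = 0.5, power at the full 0.44 is already 0.30 (change score) or 0.38 (baseline-adjusted). That drop comes from the effect-size conversion in G*Power, which is a separate issue.

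**The case against.** The protocol discloses where 0.44 comes from and describes the trial as the first comparison of its kind, so a direct estimate was probably not to hand. The Background also says that earlier exercise effects may be diluted, because participants were not necessarily fatigued at baseline and programmes were not designed around fatigue. This trial enrols only people scoring 34 or less on the FACIT-F. Part of this stands: borrowing an effect is understandable, and the pooled value need not carry over unchanged. But a larger benefit of exercise in fatigued survivors would be expected in both arms. It gives no value for the difference between them, and the Sample size section makes no such argument.

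It is also fair that 0.44 may not be far from the protocol's own threshold. Three points is 3/7 = 0.43 at an SD of 7, and 0.44 equals 3 points at an SD of 3/0.44 = 6.8. At that end of the range the justification changes more than the number does. At an SD of 10, 3 points is only 0.30.

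Three stronger readings are tempting, and the documents do not support them:

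- A reader might infer that the tailored arm must reach 0.88 SD over no exercise (0.44 + 0.44). That holds only if traditional exercise delivers exactly the pooled 0.44 in this population, which the protocol does not say.
- A reader might infer that the between-arm interval is bound to have a half-width above 3 points. At SD 7 it is 3.7 for r = 0.5 but 2.6 for r = 0.8. The mixed model may also gain something from the FACIT-F scores at weeks 3, 6 and 9, which step 3 ignores.
- A reader might infer that the protocol means to claim equivalence after a null result. It states a superiority hypothesis and proposes no such claim.

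**Conclusion.** The concern holds in a limited form. The 80% power is attached to an effect from a contrast the trial does not contain, and the protocol does not justify that effect as the increment of tailoring. The mismatch is clear from the text and needs no assumption.

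Its size does need assumptions. By the protocol's reproduced method, power at 44 completers is about 0.57, 0.30 or 0.11 for an increment of three-quarters, half or a quarter of 0.44, against 0.81 for all of it. The documents cannot say which fraction is right, so they cannot show by how much the trial is underpowered on this ground.

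Throughout the SD and correlation ranges examined, direct power for a 3-point between-arm difference stays below 0.80 (highest 0.64). Even the narrowest interval, ±2.6 points, would still include 3 points for any non-significant estimate above 3 − 2.6 = 0.4 in favour of tailoring. A non-significant result would therefore often leave a relevant benefit open.

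**What to change.** - In Sample size, stop presenting 0.44 as the expected between-arm effect. If the figure is kept, describe it as the reported effect of exercise against control.
- Restate the planning for 44 completers against a 3-point FACIT-F difference, and say in Intended statistical analysis that the 3 points apply between arms.
- State an assumed SD suited to a population restricted to scores of 34 or less, and a range of pre-post correlations. Give the resulting power and expected 95% interval width, as in the second table above.
- Commit to reporting the between-arm 95% confidence interval for the primary outcome and reading it against 3 points. The current sentence on intervals follows the text on pairwise comparisons and may not cover the primary model.

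The cost is a less favourable stated power. No participants are added and the design does not change. Enlarging the trial instead would first need a defended increment: by the protocol's reproduced method, half of 0.44 would take 166 completers, or 166 / 0.85 = 196 randomized.

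### Under ordinary assumptions, 44 participants do not give the stated 80% power for the stated SMD of 0.44; the figure matches an effect about twice as large

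*Protocol article*

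**What the plan says.** The Sample size section of the protocol article names G*Power 3 and the test: "The hypothesis was treated as a time × treatment (within-between) interaction for the primary outcome measure of score on the FACIT-F". The effect is given as follows: "A standardized mean difference of 0.44 was used, as reported in a 2012 Cochrane review for comparisons of CRF following an exercise intervention or control". The result is: "Using an α level of 0.05, a 1 - β of 0.8, the total sample size was calculated as 44". Allowing for 15% attrition, the total becomes 52. Methods/design describes a "two-armed parallel design and 1:1 allocation ratio", so 44 means 22 per arm.

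The section does not give the f value entered, the number of measurements, the correlation between them, or the G*Power effect-size option.

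Two other places bear on the analysis. Table 2 schedules FACIT-F at Lab Visit #2, weeks 3, 6 and 9, Lab Visit #4, and months 6 and 12. Intended statistical analysis plans a linear mixed model for FACIT-F between arms over time.

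**The concern.** An SMD describes a difference between two group means, whereas G*Power's interaction procedure asks for f on the scale of interaction effects. Halving d is the right conversion for a one-way comparison of two means. In a two-arm, pre-post interaction the effect is spread over four cells, and halving d overstates f by a factor of two. Because power depends on the square of f, that doubling makes the noncentrality four times too large.

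The between-arm FACIT-F comparison is the primary aim. If the stated power is wrong, a real difference of 0.44 SD could easily be missed, and readers who trust the 80% would give a non-significant result more weight than it deserves.

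**Working it through.** **Inputs from the article:** SMD 0.44, α 0.05, power 0.80, two arms at 1:1, total 44, attrition 15%.

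**Assumptions, because the article does not give them:** two measurements (m = 2) and a correlation between them of ρ = 0.5, then varied. The F test corresponds to a two-sided t test. The SMD is taken in units of the raw-score SD.

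**Step 1. Reproduce 44.** The procedure uses λ = f²·N·m/(1−ρ), with 1 and N−2 degrees of freedom when there are two arms and two times.

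- f = 0.44/2 = 0.22, N = 44: λ = 0.0484 × 44 × 2/0.5 = 8.52, power 81.4%.
- Same f, N = 42: λ = 8.13, power 79.5%.

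So 44 is the first even total to reach 80%. A second route gives the same answer: 0.44 entered directly under the Cohen option, where λ = f²·N = 0.1936 × 44 = 8.52. The attrition step is correct: 44/0.85 = 51.8, rounded up to 52.

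**Step 2. Find the f that an SMD of 0.44 implies.** Put both arms at 0 before treatment, and at d and 0 after. The grand mean is d/4. The arm means are d/2 and 0, and the time means are 0 and d/2. The interaction term for the treated-post cell is d − d/2 − d/2 + d/4 = d/4, and the other three cells are ±d/4. Hence f = d/4 = 0.11. Working backwards, f = 0.22 corresponds to d = 0.88. Under the Cohen option at ρ = 0.5, the matching entry would be 0.22 (0.0484 × 44 = 2.13), so entering 0.44 there is also a doubling.

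**Step 3. Power at N = 44 for 0.44 SD.** At ρ = 0.5, λ = 0.0121 × 44 × 2/0.5 = 2.13 and power is 29.7% (34.3% if all 52 are analysed). As a check without G*Power conventions, the SD of change is √(2(1−ρ)) = 1 at ρ = 0.5. A two-sample t test with 22 per arm then has 29.7% power at 0.44 and 81.4% at 0.88. If 0.44 were instead in change-score SD units, power would be 29.7% at any ρ.

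For other correlations, the change-score test uses d/√(2(1−ρ)), and the baseline-adjusted test uses d/√(1−ρ²):

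| ρ | Change score / interaction | Baseline-adjusted |
|---|---|---|
| 0.3 | 23% | 32% |
| 0.5 | 30% | 38% |
| 0.6 | 36% | 43% |
| 0.7 | 45% | 51% |
| 0.8 | 62% | 66% |

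The correct f = 0.11 yields 44 only at ρ = 0.875: λ = 0.0121 × 44 × 2/0.125 = 8.52.

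**Step 4. Use the repeated on-study scores.** Assume compound symmetry, four post-baseline values (weeks 3, 6, 9 and Lab Visit #4), and a difference of 0.44 SD that is already complete at week 3 and stays constant. The mean of the four has variance (1+3ρ)/4.

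- Mean minus baseline, variance (1+3ρ)/4 + 1 − 2ρ: 0.625 at ρ = 0.5, power 44%; 0.375 at ρ = 0.7, power 64%.
- Baseline-adjusted, variance (1+3ρ)/4 − ρ²: 0.375 at ρ = 0.5, power 64%; 0.285 at ρ = 0.7, power 76%.

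At ρ = 0.8 the first variance falls to 0.25, an SD of 0.5. The standardized effect is then 0.88 and power reaches 81%.

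**Step 5. Detectable difference with 22 per arm at ρ = 0.5.** For change scores, 0.86 SD gives 79.6% and 0.87 SD gives 80.5%, so about 0.87 SD. With baseline adjustment, multiply by √(1−0.25) = 0.866 to get about 0.75 SD.

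**The case against.** The strongest reply is that the mechanism is inferred. The article does not report f, the number of measurements, the correlation or the option chosen, and a condensed article may leave these to a fuller protocol. Two routes lead to 44, and only one of them is the d/2 conversion. A third, the correct f with ρ of about 0.875, cannot be excluded. This stands: the doubling is the likely explanation, not an established one.

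The second reply is that a reader might infer that the trial's power is really 30%. The documents do not support that as a single figure. It holds for a two-time-point comparison at ρ = 0.5, while the article plans a mixed model on FACIT-F measured repeatedly. Under favourable assumptions that analysis does considerably better, and with a constant early effect and ρ as high as 0.8 it would reach 80%. An effect complete by week 3 of a 12-week programme is optimistic, however, and the article states neither that assumption nor a high correlation. Across correlations of 0.5 to 0.7, power stays below 80% even on those favourable terms.

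A reader might also infer that a null result is going to be reported as proof that tailoring adds nothing. The article says no such thing. It plans 95% confidence intervals for mean differences and names a 3-point difference as clinically relevant. The risk lies in how others would read a claim of 80% power.

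**Conclusion.** The statement of 80% power for an SMD of 0.44 with 44 participants is wrong as written under ordinary assumptions. The number matches a difference of about 0.88 SD. For 0.44 SD, a pre-post comparison has about 23% to 62% power for ρ from 0.3 to 0.8 (30% at 0.5), and 38% to 66% with baseline adjustment for ρ from 0.5 to 0.8. Analysing the repeated on-study scores gives about 44% to 76% for ρ from 0.5 to 0.7, given compound symmetry and a constant early effect. For the pre-post interaction test that the section names, only an unstated correlation of about 0.875 would justify 44.

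The conclusion that power falls short rests on correlations in these ranges and on the SMD being in raw-score or change-score SD units. It does not depend on which route led to 44. Nor does it show that the trial must be enlarged: a small trial with its power honestly described is defensible.

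**What to change.** In the Sample size section:

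- State the f value, number of measurements, correlation and G*Power effect-size option that were used.
- Restate power for an SMD of 0.44 as a range over plausible correlations for the planned mixed-model analysis, with the assumed course of the effect over time.
- Give the difference detectable with 80% power at 44 evaluable participants: about 0.87 SD for change scores and about 0.75 SD with baseline adjustment, both at ρ = 0.5.
- Remove the claim of 80% power for 0.44, unless a correlation high enough to support it is stated and justified.

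In the report, do not read a non-significant result as showing that the two programmes do not differ.

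The attrition step can stay. The cost is a text correction and a less favourable power statement. No extra participants and no change in design or analysis are needed.
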